### **10.2.3 Control Group Comparison**

An institutional historical control patient cohort, which was used to determine the historical G-tube rate of 32%, will be used for comparative analyses with our study cohort.

### **10.2.4 Safety Analysis**

Toxicity will be graded using the NCI Common Toxicity Criteria for Adverse Events (CTCAE) version 4.0. AEs and SAEs will be reported using a CTCAE v4.0 terminology and severity. Given that this is a food without any known properties to interact adversely with chemoradiation for head and neck cancer, we anticipate no specific toxicities which should trigger stopping the study. However, toxicity will be monitored and a 10% rate of grade 3 or higher toxicity attributable to Soylent™ will trigger study stoppage.

### **10.3 Patient Accrual and Study Duration**

It is expected that it will take approximately 1 year to complete the study accrual. Study-related data will be stored for 5 years after termination of the study when accrual is no longer taking place and all patients have discontinued follow-up procedures.

### **10.4 Interim Analysis**

There will be one planned interim analysis for G-tube rate, when data for the primary outcome measure are available for 50% of the original sample size (30 of 60 patients planned for enrollment). We will predict the G-tube rate (and confidence interval) at the end of the study condition based on the data observed thus far and assume a continuation of this trend at the end of the study.

### **10.5 Criteria for removal from study**

10.5.1 The patient withdraws.

10.5.2 The investigator may withdraw a patient from the study for one or more of the following reasons: failure of the patient to follow instructions of the protocol study staff, the investigator decides that continuing participation could be harmful to the patient, the patient is not tolerating the Soylent™ meal replacement, the patient needs treatment not allowed in the study, the study is cancelled, other administrative reasons, or unanticipated circumstances.

10.5.3 The patients fail Swallow Preservation Program Clinical Swallow Evaluation (CSE) and Modified Barium Swallow (MBSS).

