## **5.3 Baseline Nutritional, Metabolic, & QOL Assessments**

Prior to beginning chemoradiation, baseline serum samples, cheek swab samples, body weight, and body mass index will be obtained. This may be collected at the time of consent. A panel of germ-line biomarkers predicting radiation-related toxicity will be incorporated to control for baseline differences in radiosensitivity. Baseline labs will be drawn along with necessary pre-treatment labs for chemoradiation to minimize patient inconvenience and discomfort. All patients will be asked to fill out patient-reported quality of life (QOL) questionnaires (UW-QOL and FACT-HN). All patients will have a clinical nutritional assessment by the study dietitian prior to initiating treatment or within the first week ( $\leq 5$  treatment sessions) of treatment.

All patients will participate in the Swallow Preservation Program in the Speech Pathology Clinic. They will begin participation within one week ( $\geq 5$  treatment sessions) of initiating chemoradiation. They must pass the Clinical Swallow Evaluation (CSE) that occurs during the Swallow Preservation Program initial assessment or deemed to have a functional oropharyngeal swallow with a Modified Barium Swallow Study (MBSS) if unable to pass the CSE for continuation in the study. Teaching to minimize dysphagia will be administered, and evaluation for evidence of aspiration will also be done throughout participation in the Swallow Preservation Program.

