## 10. STATISTICAL CONSIDERATIONS

### 10.1 Study Endpoints

#### 10.1.1 Sample Size and Power Consideration

This is a single arm, phase II prospective study to evaluate Soylent™ oral nutritional supplementation for compliance rate and potential impact on therapeutic G-tube rate, nutrition, quality of life, and clinical outcomes with its use during and immediately following chemoradiation in the definitive or adjuvant setting for head and neck cancer. The primary endpoints are compliance rate of Soylent™ oral nutrition supplementation and therapeutic G-tube rate. We plan to enroll 60 patients.

One primary endpoint is to ensure compliance with Soylent™ nutritional supplementation in patients undergoing concurrent chemoradiation. For feasibility in using this supplement for head and neck cancer patients, a goal of more than 50% of patients should continue to use this supplement (to at least 50% of recommended quantities) throughout treatment once initiated.

A therapeutic G-tube placement rate 33% lower than institutional historical control data is the second primary endpoint for this study. Our historical control data notes a 32% G-tube rate for chemoradiation patients, so the goal endpoint is 20%. If, conversely, a 25% higher rate of therapeutic G-tube placement occurs (equating to a 40% G-tube placement rate), this should trigger study stoppage. A sample size of 60 patients achieves 80% power to detect a 33% reduction in G-tube placement rate when comparing to historical control patients (i.e. 20% vs 32%), using a one-sided one-sample exact Binomial test, at a 0.10 significance level.

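### Section 10.5 does not separate stopping Soylent from leaving the study, so patients at risk of failing a primary endpoint can be removed after enrolment with no stated follow-up for G-tube placement

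*Protocol*

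**What the plan says.** Section 10.5 gives the criteria for removal from the study.

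- **10.5.2** leaves withdrawal to the investigator's discretion. Its grounds include "failure of the patient to follow instructions of the protocol study staff" and "the patient is not tolerating the Soylent™ meal replacement, the patient needs treatment not allowed in the study".
- **10.5.3** adds patients who fail both the Clinical Swallow Evaluation (CSE) and the Modified Barium Swallow study (MBSS), without discretionary wording.

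Section 5.3 places the swallow assessment after enrolment, around the first week of chemoradiation. A functional MBSS is needed "if unable to pass the CSE for continuation in the study".

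Section 5.4 takes a different line on patients who give up Soylent. Someone who stops for good while the dietitian still advises it counts as non-compliant. Someone who refuses to resume is offered other nutritional advice. Three reasons for stopping are exempt: aspiration, G-tube placement, and weight maintained on regular nutrition.

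The G-tube window in Section 1.1.2 opens on the first day of chemoradiation and closes four weeks after treatment. Section 10.1.1 states "We plan to enroll 60 patients" and makes no allowance for removals. Section 10.2.3 takes the 32% benchmark from an institutional historical cohort and describes no matching removals.

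**The concern.** The removal grounds are related to the primary outcomes. Not tolerating Soylent and not following instructions come close to being the compliance failure itself. Failing both swallow tests plausibly marks a patient likely to need a tube: Section 2.0 names high aspiration risk among the usual reasons for recommending one. These removals can fall inside the G-tube window.

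The protocol does not say whether removed patients are still followed for tube placement, or how they count in either endpoint. Dropping high-risk patients lowers the observed tube rate without any effect of Soylent. Counting removed patients as tube-free does the same. An analysis plan can define a denominator, but it cannot supply outcomes that nobody was told to record. In an open single-arm trial, discretionary withdrawal is a further route by which this selection can enter.

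**Working it through.** **1. The plan's own figure.** Section 10.1.1 states: "A sample size of 60 patients achieves 80% power to detect a 33% reduction in G-tube placement rate", "using a one-sided one-sample exact Binomial test, at a 0.10 significance level". The inputs are n = 60, p0 = 0.32 and p1 = 0.20. The largest count c with P(X ≤ c | 60, 0.32) ≤ 0.10 is c = 14. This gives:

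- exact type I error P(X ≤ 14 | 0.32) = 0.094 (at c = 15 it would be 0.153)
- exact power P(X ≤ 14 | 0.20) = 0.793

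The stated 80% is reproduced.

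**2. Dropping removed patients when Soylent has no effect.** Hold the true rate over all 60 at 0.32, which is 60 × 0.32 = 19.2 expected tubes. Let m patients with tube risk q be removed. The rate in the rest is

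r = (19.2 − m·q) / (60 − m).

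The exact test is then rerun at n = 60 − m. The protocol gives neither m nor q, so both are assumptions.

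| m removed | n, reject at | q | r | Type I error |
|---|---|---|---|---|
| 3 | 57, ≤ 13 | 0.32 | 0.320 | 0.086 |
| 3 | 57, ≤ 13 | 0.50 | 17.7/57 = 0.311 | 0.113 |
| 3 | 57, ≤ 13 | 0.70 | 17.1/57 = 0.300 | 0.149 |
| 3 | 57, ≤ 13 | 1.00 | 16.2/57 = 0.284 | 0.216 |
| 6 | 54, ≤ 12 | 0.32 | 0.320 | 0.079 |
| 6 | 54, ≤ 12 | 0.50 | 16.2/54 = 0.300 | 0.135 |
| 6 | 54, ≤ 12 | 0.70 | 15.0/54 = 0.278 | 0.227 |
| 6 | 54, ≤ 12 | 1.00 | 13.2/54 = 0.244 | 0.423 |

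Dropping patients of average risk does not inflate the error. Higher risk does, and even three removals at 50% risk take it past 0.10.

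**3. Counting removed patients as tube-free.** The denominator stays at 60 and the expected rate is (19.2 − m·q)/60. With m = 6 and average risk this is (19.2 − 1.92)/60 = 0.288, below 0.32. Under this rule even average-risk removals lower the rate.

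**4. Power.** With a 20% rate among those analysed, power is 0.793 at n = 60, 0.762 at n = 57 and 0.726 at n = 54.

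**5. Compliance.** The synopsis expects about 90% of patients to reach the 5% weight-loss trigger: 0.90 × 60 = 54 starters. The goal is more than 50%. As an illustration:

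- 26/54 = 48.1%, goal missed
- drop 3 non-compliers: 26/51 = 51.0%, goal met
- drop 6 non-compliers: 26/48 = 54.2%, goal met

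**6. Sections 5.4 and 10.5.2 side by side.** Section 5.4 classifies a patient who stops or refuses against advice as non-compliant and continues to advise that patient, which presumes the patient is still in the study. Section 10.5.2 lets the investigator withdraw the same patient. The protocol does not say which governs the count.

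**The case against.** A reader might infer more: that removed patients' tube outcomes are not collected, that these patients leave both denominators, and hence that both primary endpoints are already biased. The documents do not support that.

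- **Data and denominators.** Section 10.5 is silent on data collection after removal, and Section 10.2.1 names no reduced analysis set. An analysis plan not shown here may keep everyone in. The calendar has an early-termination column, follow-up is standard of care, and Section 5.4 has tubes placed at the study site. The data probably exist in routine records.
- **Discretion.** Withdrawal under 10.5.2 is optional, so the criteria permit these removals but do not compel them.
- **Compliance.** Section 5.4 already counts most of the patients concerned as non-compliant. Bias arises only if 10.5.2 overrides it.
- **Swallow tests.** Failure of both tests is required, and clinically significant dysfunction is excluded at consultation, so such removals may be few. They hardly touch compliance, which is judged once Soylent has been started and exempts aspiration.
- **Benchmark.** How the historical cohort was selected is not described. One cannot say that it had no comparable exclusions, only that none is stated.
- **Size.** The 0.42 needs six removals, all of whom would have been tubed. Power is reduced, not lost.

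All of this stands, and it makes the bias conditional. What remains is that the protocol sets out removal from the study on outcome-related grounds, does not say that G-tube follow-up continues, and leaves two sections in conflict.

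**Conclusion.** The point holds as a conditional weakness that should be fixed; confidence is medium. Section 10.5 as written allows outcome-related removal after enrolment, within the G-tube window, without requiring that the outcome still be recorded.

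The G-tube endpoint is the more exposed. The inflated error rates apply if there is no true effect, removed patients are dropped, and their tube risk is 50% or more. The compliance exposure is narrower and depends on 10.5.2 prevailing over 5.4. The numbers removed, their tube risk and the 26 compliers are illustrative assumptions. Bias in either endpoint is not demonstrated.

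**What to change.** Amend the wording in three places.

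1. In Section 10.5, distinguish stopping Soylent from removal from the study.
2. State that every enrolled patient who starts chemoradiation stays in the G-tube denominator, whatever happens with Soylent or the swallow tests. Follow each of them from routine records to four weeks after treatment unless consent is withdrawn.
3. Reconcile 10.5.2 with 5.4: patients who started Soylent and are withdrawn for intolerance or non-adherence stay in the compliance denominator as non-compliant. Leave the three exemptions in 5.4 as they are.

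Clinical decisions about stopping Soylent are not affected. The cost is a protocol amendment and chart review of follow-up that is already routine. The downside is that both rates may look slightly less favourable.

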## 1. Appendix.

soylent

Login

Checkout.

Login for a faster checkout.

Shipping.

Free shipping to the continental United States and Canada on orders greater than \$20.  
More countries coming soon.

Country

United States

Full name

Address Line 1

Address Line 2 (Optional)

City

State

Alabama

Zipcode

Phone (Optional)

Payment.

Card number

Expiration month

01 (January)

Expiration year

2016

Create an account.

An account is needed for checkout. Already have an account? Login.

Full Name

Email

Password

☒ I'm awesome, email me about cool stuff. (Optional)

Total (USD)

\$32.30

Renews on 1/9/2017 for \$32.30/month

Purchase Soylent

This is it, your order will be on the way.

Order Summary

Soylent Drink

\$32.30/month

Delivered to 3-7 business days

12 Bottles

Original Price ..... \$34

Shipping ..... Free

Subscription Savings ..... -\$1.70

Total (USD) \$32.30

Renews on 1/9/2017 for \$32.30/month

Coupon (Optional) 

Apply Coupon

Go back to the products page to continue shopping.

**Soylent intake of product (Compliance)**

| Sunday
Date:                                                                                                                                                                                               | Monday
Date:                                                                                                                                                                                               | Tuesday
Date:                                                                                                                                                                                              | Wednesday
Date:                                                                                                                                                                                            | Thursday
Date:                                                                                                                                                                                             | Friday
Date:                                                                                                                                                                                               | Saturday
Date:                                                                                                                                                                                             |
|---------------------------------------------------------------------------------------------------------------------------------------------------------------------------------------------------------------|---------------------------------------------------------------------------------------------------------------------------------------------------------------------------------------------------------------|---------------------------------------------------------------------------------------------------------------------------------------------------------------------------------------------------------------|---------------------------------------------------------------------------------------------------------------------------------------------------------------------------------------------------------------|---------------------------------------------------------------------------------------------------------------------------------------------------------------------------------------------------------------|---------------------------------------------------------------------------------------------------------------------------------------------------------------------------------------------------------------|---------------------------------------------------------------------------------------------------------------------------------------------------------------------------------------------------------------|
|  Breakfast
 _____
 Lunch
 _____
 Dinner
 _____ |  Breakfast
 _____
 Lunch
 _____
 Dinner
 _____ |  Breakfast
 _____
 Lunch
 _____
 Dinner
 _____ |  Breakfast
 _____
 Lunch
 _____
 Dinner
 _____ |  Breakfast
 _____
 Lunch
 _____
 Dinner
 _____ |  Breakfast
 _____
 Lunch
 _____
 Dinner
 _____ |  Breakfast
 _____
 Lunch
 _____
 Dinner
 _____ |
| Comments                                                                                                                                                                                                      | Comments                                                                                                                                                                                                      | Comments                                                                                                                                                                                                      | Comments                                                                                                                                                                                                      | Comments                                                                                                                                                                                                      | Comments                                                                                                                                                                                                      | Comments                                                                                                                                                                                                      |
|                                                                                                                                                                                                               |                                                                                                                                                                                                               |                                                                                                                                                                                                               |                                                                                                                                                                                                               |                                                                                                                                                                                                               |                                                                                                                                                                                                               |                                                                                                                                                                                                               |
| Sunday
Date:                                                                                                                                                                                               | Monday
Date:                                                                                                                                                                                               | Tuesday
Date:                                                                                                                                                                                              | Wednesday
Date:                                                                                                                                                                                            | Thursday
Date:                                                                                                                                                                                             | Friday
Date:                                                                                                                                                                                               | Saturday
Date:                                                                                                                                                                                             |
|  Breakfast
 _____
 Lunch
 _____
 Dinner
 _____ |  Breakfast
 _____
 Lunch
 _____
 Dinner
 _____ |  Breakfast
 _____
 Lunch
 _____
 Dinner
 _____ |  Breakfast
 _____
 Lunch
 _____
 Dinner
 _____ |  Breakfast
 _____
 Lunch
 _____
 Dinner
 _____ |  Breakfast
 _____
 Lunch
 _____
 Dinner
 _____ |  Breakfast
 _____
 Lunch
 _____
 Dinner
 _____ |
| Comments                                                                                                                                                                                                      | Comments                                                                                                                                                                                                      | Comments                                                                                                                                                                                                      | Comments                                                                                                                                                                                                      | Comments                                                                                                                                                                                                      | Comments                                                                                                                                                                                                      | Comments                                                                                                                                                                                                      |
|                                                                                                                                                                                                               |                                                                                                                                                                                                               |                                                                                                                                                                                                               |                                                                                                                                                                                                               |                                                                                                                                                                                                               |                                                                                                                                                                                                               |                                                                                                                                                                                                               |
| Sunday
Date:                                                                                                                                                                                               | Monday
Date:                                                                                                                                                                                               | Tuesday
Date:                                                                                                                                                                                              | Wednesday
Date:                                                                                                                                                                                            | Thursday
Date:                                                                                                                                                                                             | Friday
Date:                                                                                                                                                                                               | Saturday
Date:                                                                                                                                                                                             |
|  Breakfast
 _____
 Lunch
 _____
 Dinner
 _____ |  Breakfast
 _____
 Lunch
 _____
 Dinner
 _____ |  Breakfast
 _____
 Lunch
 _____
 Dinner
 _____ |  Breakfast
 _____
 Lunch
 _____
 Dinner
 _____ |  Breakfast
 _____
 Lunch
 _____
 Dinner
 _____ |  Breakfast
 _____
 Lunch
 _____
 Dinner
 _____ |  Breakfast
 _____
 Lunch
 _____
 Dinner
 _____ |
| Comments                                                                                                                                                                                                      | Comments                                                                                                                                                                                                      | Comments                                                                                                                                                                                                      | Comments                                                                                                                                                                                                      | Comments                                                                                                                                                                                                      | Comments                                                                                                                                                                                                      | Comments                                                                                                                                                                                                      |
|                                                                                                                                                                                                               |                                                                                                                                                                                                               |                                                                                                                                                                                                               |                                                                                                                                                                                                               |                                                                                                                                                                                                               |                                                                                                                                                                                                               |                                                                                                                                                                                                               |
| Sunday
Date:                                                                                                                                                                                               | Monday
Date:                                                                                                                                                                                               | Tuesday
Date:                                                                                                                                                                                              | Wednesday
Date:                                                                                                                                                                                            | Thursday
Date:                                                                                                                                                                                             | Friday
Date:                                                                                                                                                                                               | Saturday
Date:                                                                                                                                                                                             |
|  Breakfast
 _____
 Lunch
 _____
 Dinner
 _____ |  Breakfast
 _____
 Lunch
 _____
 Dinner
 _____ |  Breakfast
 _____
 Lunch
 _____
 Dinner
 _____ |  Breakfast
 _____
 Lunch
 _____
 Dinner
 _____ |  Breakfast
 _____
 Lunch
 _____
 Dinner
 _____ |  Breakfast
 _____
 Lunch
 _____
 Dinner
 _____ |  Breakfast
 _____
 Lunch
 _____
 Dinner
 _____ |
| Comments                                                                                                                                                                                                      | Comments                                                                                                                                                                                                      | Comments                                                                                                                                                                                                      | Comments                                                                                                                                                                                                      | Comments                                                                                                                                                                                                      | Comments                                                                                                                                                                                                      | Comments                                                                                                                                                                                                      |
|                                                                                                                                                                                                               |                                                                                                                                                                                                               |                                                                                                                                                                                                               |                                                                                                                                                                                                               |                                                                                                                                                                                                               |                                                                                                                                                                                                               |                                                                                                                                                                                                               |

Additional comments:

|  |
|--|
|  |
|  |

